
### BBS Component

#### Overview

The BBS is an expansion to the standard PBS method and was led by the study teams’ clinical officers and HTS counselors. It comprised 2 data collection methods: individual, structured interviews and biological sample collection (Table 1). Importantly, in the context of this study’s objectives and research questions, data from the BBS provide critical information to describe treatment and program coverage outcomes for the study population. BBS data are only linkable to PBS data at the group level.

**Table 1 table1:** Biological samples collected from female sex workers and men who have sex with men during the biobehavioral survey in Nairobi, Kenya, from April to May 2023.

Biomarkers	Sample type	Type of test	Test location
HIV diagnosis	Capillary blood	Rapid test	Study site
Recency of HIV infection	Plasma	Laboratory-based test	PHDA^a^ laboratory
HIV-1 RNA viral load	Plasma	Laboratory-based test	PHDA laboratory
Actively taking PrEP^b^	Urine	Rapid test	Study site or in the PHDA laboratory

^a^PHDA: Partners for Health and Development in Africa.

^b^PrEP: pre-exposure prophylaxis.

#### Individual, Face-to-Face Structured Interviews

Following the PBS, all participants who provided informed consent participated in a brief, face-to-face, structured interview with a clinical officer to gather limited demographic information, basic behavioral information related to HIV risk, and program access and service use data. These data will be linked, at the individual level, to biological samples (blood and urine), which were collected following the face-to-face interviews.

#### Biological Samples

##### Urine Sample

To protect the confidentiality of participants’ HIV status, urine samples were collected from all participants who provided informed consent to providing biological samples. However, only samples from those participants who had reported currently taking PrEP in the preceding face-to-face interview underwent testing using a rapid tenofovir assay developed and validated by the University of California, San Francisco in conjunction with Abbott Laboratories [24]. Depending on timing and the facilities available on-site, the samples were either tested for tenofovir at the study site or sent to the PHDA laboratory for processing the following day (Table 1).

##### Blood Samples

HTS counselors collected fingerprick blood samples from all participants who provided informed consent for on-site rapid HIV testing. Following Kenyan rapid testing algorithms, Determine HIV-1 or HIV-2 (Abbott Diagnostic Medical Co Ltd) was used as the initial screening assay. All reactive samples underwent confirmatory testing using First Response (Premier Medical Corp Ltd) rapid tests. Pre- and posttest counseling sessions were administered to all participants undergoing HIV rapid testing in accordance with the national guidelines [25].

In addition, clinical officers drew 5 mL venous blood samples from consenting participants who tested positive for HIV in the rapid test. Whole blood samples were transferred to the PHDA laboratory for further analyses, including HIV viral load and recency testing (Table 1). The HIV viral load analyses will be conducted using GeneXpert HIV-1 Viral Load Kits (Cepheid). HIV recency will be determined using the Asante HIV-1 Rapid Recency Assay (Sedia Biosciences Corporation). All laboratory-based tests will be carried out in accordance with the PHDA laboratory’s standard operating procedures and in adherence to the national guidelines [26].

##### Biological Sample Management

All specimens, both urine and blood, were affixed with preprinted standard codes along with the corresponding survey identification at the time of collection. Following collection, all biological samples were carefully placed in boxes at room temperature. These samples were transported to the PHDA laboratory using PHDA vehicles for processing and subsequent testing. The transfer of samples from study sites to the PHDA laboratory followed a protocol outlined by the PHDA laboratory’s standard operating procedures. Both urine and blood samples will be maintained at a temperature of −80°C for 5 years within the PHDA laboratory per standard operating procedures. This extended storage period ensures the availability of samples for the confirmation of any discrepant laboratory results that may arise over time. Stored specimens will not be linked to any personal identifiers and cannot be traced back to the individuals who provided them, preserving the confidentiality and privacy of the participants.

### FGD Component

The FGD component of the ePBS study was led by the study teams’ qualitative researchers. For each key population group, participants were selected from every fifth PBS session and were engaged in the FGD after providing informed consent. Each FGD consisted of the same 10 to 12 participants who participated in the preceding PBS session. The FGDs were facilitated by trained qualitative researchers using an FGD guide. The discussions were conducted in either Kiswahili or Sheng, which is a local slang language predominantly spoken in urban areas of Kenya, particularly Nairobi. All FGDs were audio recorded and will be translated and transcribed verbatim for analysis.

### Participant Inclusion Criteria

To be eligible for participation in this ePBS study, female sex workers had to be assigned female at birth, aged at least 18 years, and acknowledge having received money or gifts in exchange for sexual intercourse with an individual assigned male at birth at least once in the past 3 months. Eligible men who have sex with men had to be assigned male at birth, aged at least 18 years, and report at least 1 anal sex act (insertive or receptive) with another individual assigned male at birth in the past 3 months. To be eligible, all participants had to be capable and willing to provide written or verbal informed consent to participate in the 3 components of the ePBS study, self-identify as a sex worker or a man who has sex with other men, and report actively practicing sex work or cruising within Nairobi County.

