### ePBS Method

The ePBS method is a rapid, cross-sectional study design using complementary quantitative and qualitative methods for data collection. The innovative approach expands upon the traditional polling booth survey (PBS) method [19] by incorporating additional qualitative, quantitative, and biological data collection methods and an improved population-based approach to random sampling. Within the ePBS method, quantitative methods include (1) PBS, a group interview method in which individuals provide anonymous and unlinked responses to survey questions through a ballot, which has been shown to reduce reporting and social desirability biases for sensitive questions about conventionally stigmatizing behaviors, experiences, and social circumstances [19,20] and (2) behavioral and biological survey (BBS), which includes a short face-to-face, individual interview linked to the collection of biological samples (blood and urine). Qualitative methods include FGD with a subset of ePBS participants to inquire about factors that contribute to gaps in program coverage. Hence, the expansion of the traditional PBS by adding a BBS and FGD is referred to as ePBS.

Cross-sectional designs are commonly used for population-based surveys and to assess the prevalence of diseases in a population [21]. They are also useful for informing planning, monitoring, and evaluation of public health programs and interventions. In this study, we use quantitative methods to measure prevention program outputs and relevant outcomes among female sex workers and men who have sex with men participants, as outlined in research questions 1 to 3. We use qualitative methods to gain insight into the barriers affecting the accessibility and use of HIV services, as specified in research question 4.

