For each key population group, participants in every fifth PBS session were invited to participate in an FGD. In total, 20 FGDs were conducted with ePBS participants (female sex workers: *n*=13, 65%; men who have sex with men: n=7, 35%).

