### Ethical Considerations

#### Informed Consent

At the data collection site, before ePBS data collection commenced, prevention officers, with the support of community researchers, guided participants through the informed consent process, ensuring that all participants understood and were comfortable with the information included in the consent form. Any questions from potential participants were addressed before commencing the study. Nonconsenting or unwilling participants were thanked for their time and excluded from the study. All eligible participants who provided written or verbal informed consent received a unique identifying code that was used for the BBS portion of the study.

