## Results

The study enrolled 759 female sex workers (response rate: 759/769, 98.6%) and 398 men who have sex with men (response rate: 398/420, 94.7%) across 64 and 35 PBS sessions, respectively (Table 2).

In total, 758 (99.9%) female sex workers (1 participant refused participation in BBS) and 398 (100%) men who have sex with men participated in the face-to-face interview for the BBS, and all (n=1156) provided blood and urine samples for rapid tests. In total, 14.79% (171/1156) of participants (female sex workers: n=101, 59.1%; men who have sex with men: n=70, 40.9%) tested positive for HIV via rapid test. Among those testing positive, 93.6% (160/171) of participants (female sex workers: n=100, 62.5%; men who have sex with men: n=60, 37.5%) provided consent for venous blood sample collection. Three whole blood samples from female sex worker participants were discarded due to missing bar codes on the sample tubes. A total of 73 participants reported currently receiving PrEP in the BBS face-to-face interview (Table 2), and rapid urine tests were conducted on the samples from these participants (female sex workers: n=56, 77%; men who have sex with men: n=17, 23%).

**Table 2 table2:** Expanded polling booth survey (ePBS) participant enrollment and data collection among female sex workers and men who have sex with men in Nairobi County, Kenya, from April to May 2023 (n=1157).

	Female sex workers (n=759), n (%)	Men who have sex with men (n=398), n (%)
PBS participants	759 (100)	398 (100)
BBS^a^ participants	758 (99.9)	398 (100)
HIV rapid tests conducted	758 (99.9)	398 (100)
Reactive HIV rapid test results	101 (13.3)	70 (17.6)
Venous blood samples collected	100 (13.2)	60 (15.1)
Urine tests conducted	56 (7.4)	17 (4.3)

^a^BBS: behavioral and biological survey.

A total of 20 FGDs were completed with female sex workers (n=14, 70%) and men who have sex with men (n=6, 30%).

Data cleaning and analysis are ongoing. Aggregate responses from each PBS session and individual data from BBS respondents have been entered into separate data modules in the data entry software. The data will then be exported to SPSS (version 28.0; IBM Corp) for analysis. Weights will be applied to data during analyses to account for the sampling design and to adjust for unequal selection probabilities. CIs will be calculated, and descriptive analyses of the PBS and BBS data will be performed separately to address the study objectives.

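### Eligibility requires willingness to join all 3 components, which conflicts with the component-level consent described elsewhere and, so far as it was applied, loses people unwilling to test from the anonymous survey and from any nonresponse count

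*Protocol article*

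**What the plan says.** The Participant Inclusion Criteria list sex at birth, age, recent behaviour, self-identification and activity in Nairobi. They add that a person must be "willing to provide written or verbal informed consent to participate in the 3 components of the ePBS study". The ePBS Method section identifies the components: "Hence, the expansion of the traditional PBS by adding a BBS and FGD is referred to as ePBS". The BBS comprises an interview plus blood and urine samples, and of the focus groups the FGD Component section says "All FGDs were audio recorded". Under Informed Consent, "Nonconsenting or unwilling participants were thanked for their time and excluded from the study".

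Other sections read differently. Under Biological Samples, urine, fingerprick and venous blood each come from those who consented to that procedure. The FGD has its own consent step (FGD Component) and its own invitation: "For each key population group, participants in every fifth PBS session were invited to participate in an FGD". In the Results, "1 participant refused participation in BBS", yet she stays among the 759 enrolled. The response rates there are 759/769 and 398/420, and 769 and 420 are the target sample sizes from the sample size section.

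**The concern.** Willingness to be HIV tested is not part of belonging to either key population. Placed among the eligibility criteria, it makes a person who would use the anonymous ballot but not take the test ineligible for everything, including the ballot. The PBS is in the design because anonymity helps people report sensitive matters honestly, so it is the component most able to capture those who avoid testing.

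The trait selected on also lies close to what is measured. Routine HIV testing and utilization coverage are listed outcomes, and the third objective concerns barriers to using services. If the rule removed people who use services less, testing and coverage would look better than they are and some of the gaps sought would be hidden. The planned weights deal with sampling design and selection probabilities and cannot restore people classed as outside the population. The Limitations section does not mention this selection.

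**Working it through.** **1. The passages side by side**

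- All components required: Participant Inclusion Criteria (willingness for all 3) and Informed Consent (unwilling people leave the study).
- Component by component: Biological Samples (consent tied to each sample), FGD Component (own consent), Target Sample Size Calculation (separate FGD invitation), Results (BBS refuser retained).
- Also in the Results: 171 participants tested positive and 160 gave venous blood, so 171 − 160 = 11 gave none (101 − 100 = 1 woman, 70 − 60 = 10 men) and stayed enrolled.

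Both sets cannot describe one rule applied as written.

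**2. Reach of the FGD condition**

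There were 64 + 35 = 99 PBS sessions and 20 FGDs, and 20/99 = 20.2%. Read literally, the criterion asked participants in the other 79 of 99 sessions (79.8%) to be willing to join a component they were not going to be offered.

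**3. What the response rates show**

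759/769 = 98.7% and 398/420 = 94.8% (printed as 98.6% and 94.7%, apparently truncated). The denominators are targets, not people approached or found eligible. Anyone turned away, whether called ineligible or nonconsenting, appears in neither numerator nor denominator.

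**4. Uptake among the enrolled**

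Rapid tests: 758/759 = 99.9% and 398/398 = 100%. Selection on willingness to test would produce this, but so would high acceptance without selection. It does not discriminate between the two.

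**5. Illustrative size for routine testing**

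Let f be the share of otherwise eligible people lost, t0 the share of them recently tested, and T the share tested among the enrolled. The true share is (1 − f)T + f·t0, and the overstatement is f(T − t0). T = 82% is the 2017 Nairobi figure in the Introduction, used as a stand-in. f and t0 are assumptions, since the article gives neither.

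| f | t0 | True share | Overstatement |
|---|---|---|---|
| 5% | 50% | 0.95 × 82 + 0.05 × 50 = 80.4% | 1.6 points |
| 15% | 50% | 0.85 × 82 + 0.15 × 50 = 77.2% | 4.8 points |

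The bias is zero at t0 = 82% and reverses above that.

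Bounds with no assumption on t0 (from 0% to 100%):

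- f = 5%: 0.95 × 82 = 77.9% to 77.9 + 5 = 82.9%
- f = 15%: 0.85 × 82 = 69.7% to 69.7 + 15 = 84.7%

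**The case against.** The best reply is that the described procedure separates eligibility from willingness. Under Participant Enrollment, peer educators and outreach workers assess eligibility first, eligible people then receive detailed information, and those interested go to the site. Consent is taken there, and the Informed Consent section speaks of eligible participants who consented. On that account the criterion is loose consent wording, and the retained BBS refuser and the 11 participants without venous samples show that it was not strictly enforced. This stands as evidence about enforcement. It does not remove the conflict: the criterion is printed as an eligibility condition, and unwilling people are still said to leave the whole study.

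Three further points stand.

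- The direction of bias is conditional. Some people may decline because they tested recently or already know that they are positive and are in care.
- A person who refuses the test has no HIV result under any eligibility wording, so bias in prevalence from test refusal is not specific to this rule. The harm specific to it is loss from the PBS and FGD and from the nonresponse count.
- Data collection is over, so eligibility cannot be changed for this round, and a condensed article would not normally show screening records.

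A reader might go further and infer that test-avoiders were in fact screened out, that the sample is enriched for testers, and that near-complete test uptake proves it. The documents do not support that. No passage reports anyone turned away for declining a test or a recording.

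**Conclusion.** The point holds as a contradiction to be reconciled and as a conditional selection problem. As written, the criterion and the exclusion of unwilling people lose those who would answer the PBS but refuse testing or recording, and the reported response rates cannot reveal how many there were. If such people test less often than the enrolled, routine testing and service use are overstated.

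The size is unknown and could be nil. The figure of about 2 to 5 points for recent testing rests wholly on three assumptions: 5% to 15% lost, 50% of them recently tested, and 82% tested among the enrolled. Neither the extent of enforcement nor the direction of bias is established. The matter still deserves correction because the article claims representativeness by geography and location typology, cites a high response rate as a sign of credibility, and intends the method for scale-up, which would carry the criterion with it.

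**What to change.** - **Wording:** define eligibility by population membership only (sex at birth, age, behaviour in the past 3 months, self-identification, active in Nairobi County). State consent separately for PBS, interview, rapid test, urine, venous blood and, in selected sessions only, FGD. Bring the inclusion criteria, consent text and Results into agreement, and say which rule was used in the field.
- **Existing data:** use screening records to count people turned away only for unwillingness as eligible nonrespondents. Report participation by component on those eligible and approached, not on the target size. Give routine testing with simple bounds for decliners, as in the last step of the working.
- **If the records do not allow this:** state in the Limitations that the estimates apply to people willing to take part in all components, including HIV testing, and do not cite 98.6% and 94.7% as response rates.

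The cost is a text revision and reclassification of any records held, with no new data collection. The downside is that participation will look less favourable and the PBS and BBS denominators may differ slightly.

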### Target Sample Size Calculation

To be representative of each key population group, the study’s sampling strategy was based on probability sampling techniques that provided an equal chance to all members of the study populations, meeting defined inclusion criteria, to be included in the study. The determination of an appropriate sample size for a single study domain is usually based on the following considerations: (1) the number of measurement units in the population, (2) the parameter of interest, and (3) the degree of confidence by which the parameter is estimated and the desired level of precision.

One objective of our study was to estimate the HIV prevalence and incidence among female sex workers and men who have sex with men in Nairobi County. As such, sampling parameters were set with the prevalence and sample size having 95% statistical confidence, with a desired precision of +5% or –5%.

The sample size for PBS and BBS study was calculated using the following formula: *n* = [1.96^2^*p*(1 – *p*)(*DEFF*)]/*d*^2^. Where *p* is HIV prevalence, *DEFF* is the design effect of the sampling approach, and *d* is the desired precision.

The finite population correction factor is then applied to the derived sample size using the following formula: *nf* = (*n **
*N*)/[(*n* + (*n* – 1)]. Where *nf* is the sample size adjusted for finite population correction, *n* is the sample size required, and *N* is the population size.

To calculate the sample size for this ePBS study, we used the most recent estimate of HIV prevalence among female sex workers (26%) and men who have sex with men (12%) in Nairobi, as reported in a 2017 study conducted by NASCOP [7]. The sample size calculation was adjusted to accommodate an anticipated nonresponse rate of 15%. The final target sample size, adjusted for population size and nonresponse, for female sex workers was n=769 and for men who have sex with men was n=420. Ideally, each PBS session comprises 10 to 12 participants; the total target sample sizes for female sex workers and men who have sex with men were divided by 12 to determine the total number of PBS sessions required for each key population group, that is, 64 PBS sessions with female sex workers and 35 sessions with men who have sex with men.

For each key population group, participants in every fifth PBS session were invited to participate in an FGD. In total, 20 FGDs were conducted with ePBS participants (female sex workers: *n*=13, 65%; men who have sex with men: n=7, 35%).

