In 2020, a nationwide mapping and population size estimation exercise estimated that there were 197,096 female sex workers and 61,650 men who have sex with men living in Kenya (National AIDSSTI Control Programme, unpublished data, December 2020). Approximately 20% of key populations are concentrated in Nairobi County, the largest of the 47 counties in Kenya [6]. Findings from a 2017 national study underscore the high prevalence of HIV among female sex workers and men who have sex with men in Nairobi, with self-reported rates of 22% and 27%, respectively [7]. In the same study, 91% of female sex workers in Nairobi reported using condoms with their last client, while 81% of men who have sex with men reported condom use during last anal sex [7]. Furthermore, peer educators played a significant role in outreach efforts, with 88% of female sex workers and 76% of men who have sex with men reporting contact with a peer educator within the last 3 months. The majority (82%) of both groups had undergone HIV testing within the last 3 months, while 22% of female sex workers and 27% of men who have sex with men reported that they were living with HIV. However, only 65% of female sex workers and 68% of men who have sex with men living with HIV reported being enrolled in antiretroviral therapy programs. Notably, 56% of female sex workers and 18% of men who have sex with men reported experiencing incidents of police violence within the last 6 months, respectively [7].

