HIV prevention programs for key populations in Nairobi County are implemented by several partner organizations, all of whom report to the county government and the National Key Population Program, led by the Kenyan Ministry of Health, on a monthly basis (National AIDS and STI Control Programme, unpublished data, September 2023). Having up-to-date, representative, and robust data on key populations is of paramount importance for effective planning, management, and monitoring of programs and interventions aimed at addressing their needs [8]. The most recent population-based behavioral survey conducted among key populations in Nairobi dates back to 2017 [7] and did not include biological data. The absence of recent biobehavioral data among key population groups limits the ability of both county and national programs to understand the current epidemiologic situation, assess the impact of investments in HIV prevention and treatment programs for key populations, and identify gaps in program coverage. The high cost and resource requirements for implementing nationally representative, population-based integrated biobehavioral surveillance surveys factor into the relative infrequency of their deployment [8]. The availability of methods that can efficiently collect timely data among key population groups at appropriate scale and relatively low cost across diverse contexts is extremely limited [9]. Striking a balance between the need for methodological rigor and practical, adaptable approaches that are accessible to countries with diverse income levels is a pressing requirement [10].

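### The sample size rests on 26% and 12% HIV prevalence, but the Background gives 22% and 27% from the same reference; the ±5-point target for men who have sex with men is supported only near 12%

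*Protocol article*

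**What the plan says.** Target Sample Size Calculation sizes the study on HIV prevalence, with parameters "having 95% statistical confidence, with a desired precision of +5" percent in either direction. The prevalence inputs are "the most recent estimate of HIV prevalence among female sex workers (26%) and men who have sex with men (12%) in Nairobi", credited to the 2017 NASCOP study, reference 7. After finite population correction and an allowance of 15% for nonresponse, the targets are 769 female sex workers (FSW) and 420 MSM, or 64 and 35 sessions. A design effect appears in the formula, but no value is given.

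The Background also cites reference 7, the same year and the same city. It states twice, as self-reported figures, that "22% of female sex workers and 27% of men who have sex with men reported that they were living with HIV". It then says that the 2017 survey, again reference 7, "did not include biological data".

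**The concern.** One cited source is given two different pairs of prevalence for the same city and populations, and nothing in the article explains the difference. The MSM planning figure is less than half the Background figure, and the ranking of the two groups reverses: FSW are higher in one pair, MSM in the other. If the 2017 survey took no biological samples, the second pair cannot be a biomarker result from it.

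This matters because one of the pairs is the design input. Required sample size is proportional to p(1−p), so a low p gives a small sample. If MSM prevalence is above 12%, the interval will be wider than planned unless the design effect is smaller than planned. The article also presents the method for scale-up elsewhere, so others may copy the calculation.

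**Working it through.** **Inputs.** Prevalence 26% and 12%, half-width d = 0.05, z = 1.96 and nonresponse 15% come from Target Sample Size Calculation. Population sizes of 39,227 FSW and 15,271 MSM come from Study Setting. Enrolment (759 and 398) and 70 reactive tests among 398 MSM (17.6%, unweighted) come from Results. The design effect (DEFF) is an assumption, solved from the targets.

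**Formulae.** n = 1.96² p(1−p) DEFF / d²; nf = nN / (N + n − 1); target = nf / 0.85. The correction is printed with denominator n + (n − 1). That would give about 7,600 for MSM, so it is read here as a misprint for N + (n − 1).

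**Reproducing the plan's targets.** Solving for DEFF gives 2.248 from the FSW target and 2.253 from the MSM target. With DEFF = 2.25:

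| Group | p | n | nf | nf / 0.85 | Stated |
|---|---|---|---|---|---|
| FSW | 0.26 | 665.2 | 654.1 | 769.6 | 769 |
| MSM | 0.12 | 365.1 | 356.6 | 419.5 | 420 |

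Inflating by 1.15 instead of dividing by 0.85 needs a DEFF of about 2.30. A DEFF of 2.0 gives 685 and 374 and does not reproduce the targets.

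**Which pair was used.** This check needs only a common DEFF, not its value. The targets have ratio 769/420 = 1.83. The planning pair gives (0.26 × 0.74)/(0.12 × 0.88) = 1.82. The Background pair gives (0.22 × 0.78)/(0.27 × 0.73) = 0.87. So 26% and 12% were used.

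**MSM at 27%.** n = 681.5, nf = 652.4, target = 767.5, or about 768 (64 sessions of 12), against 420 (35 sessions).

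**Half-width with 398 MSM.** 1.96 × √[p(1−p) × DEFF/n × (N−n)/(N−1)], where (15,271 − 398)/15,270 = 0.974. In percentage points:

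| DEFF | p = 12% | p = 17.6% | p = 27% |
|---|---|---|---|
| 1.0 | 3.2 | 3.7 | 4.3 |
| 1.5 | 3.9 | 4.5 | 5.3 |
| 2.0 | 4.5 | 5.2 | 6.1 |
| 2.25 | 4.7 | 5.5 | 6.5 |
| 2.5 | 5.0 | 5.8 | 6.8 |

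Setting the half-width to 5 points, the largest DEFF that still meets the target is 2.52 at 12%, 1.83 at 17.6% and 1.35 at 27%.

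**FSW.** With 759 enrolled and DEFF 2.25, the half-width is ±4.6 at 26% and ±4.4 at 22%. Both are inside the target.

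**Other MSM figures in the article.** The Background gives 18.9% nationally, from other references; at DEFF 2.25 and n = 398 that means ±5.7. So 12% is the lowest of the four MSM figures given: 12%, 17.6%, 18.9% and 27%.

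**The case against.** A reader might infer that the ±5 points is not delivered for MSM, or that 12% is the wrong figure. The documents support neither.

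- The article does not show which pair reference 7 reports. If 12% is right, 398 MSM give ±4.7 and the target is met. The article also describes ±5 as a desired precision, which is a planning goal and not a claim about the result.
- The 27% scenario sits poorly with the study's own data. At DEFF 2.25, 17.6% ± 5.5 runs from 12.1% to 23.1%. That excludes 27%, while 12% lies just below the lower limit. At 17.6% the excess over ±5 is about half a point.
- Even that half point depends on a planning DEFF. With 398/35 = 11.4 participants per session, and the whole DEFF attributed to clustering, 2.25 implies an intracluster correlation of (2.25 − 1)/(11.4 − 1) = 0.12. A realised value of about (1.83 − 1)/10.4 = 0.08 would meet ±5. The realised value could also be higher.
- The 18.9% is national, and the 17.6% was not available at planning. Neither shows that 12% was a poor choice at the time.
- Sample size affects the width of the interval and does not bias the estimate. Results already plans design weights and CIs, so realised precision will be known.

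All of this stands, and it limits the point to a conditional one. It does not remove the contradiction: two stated pairs from one reference conflict, and one of them set the sample size. That is not detail left to a fuller document.

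**Conclusion.** The inconsistency is established from the article alone: 26% and 12% in one section, 22% and 27% in another, same reference, city and year, with no explanation. That 26% and 12% produced the targets is shown by the ratio check, given a DEFF common to both groups.

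The effect on precision is conditional. It rests on a DEFF of about 2.25, inferred from the two targets, and on the unknown true prevalence. On that basis the ±5-point target for MSM is supported near 12%, missed by about half a point at 17.6%, and missed by about 1.5 points at 27%. FSW precision is not at risk under either pair. This should be corrected, but it does not undermine the study.

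**What to change.** Check the 2017 source and correct whichever prevalence pair or citation is wrong, in the Background and in Target Sample Size Calculation. If both pairs are genuine, say what each one measures and why 26% and 12% were used. State the DEFF that was used.

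Keep ±5 points as the planning target, and add that expected MSM precision depends on prevalence: about ±5.5 at 17.6% and up to about ±6.5 at 27%, if the DEFF was 2.25. The design-based CIs already planned in Results will then show the realised precision.

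The cost is a few sentences, and the stated MSM precision becomes slightly less favourable. No extra enrolment and no change of analysis is needed.
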